**Methods/design:**

The PETRA study is a randomized, controlled intervention trial investigating the effects of a yearlong partly supervised mixed exercise intervention (endurance and resistance exercises, 3–5 times per week) in 256 patients during and after allogeneic stem cell transplantation. Patients in the control group perform progressive muscle relaxation training (Jacobsen method) with the same frequency. Main inclusion criterion is planned allo-HCT. Main exclusion criteria are increased fracture risk, no walking capability or severe cardiorespiratory problems. Primary endpoint is overall survival after two years; secondary endpoints are non-relapse mortality, median survival, patient reported outcomes including cancer related fatigue and quality of life, physical performance, body composition, haematological/immunological reconstitution, inflammatory parameters, severity of complications and side-effects (e.g. GvHD and infections), and cognitive capacity.

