### Outcome measures

The outcome measures used in the PETRA study are summarized in Table 1.

**Table 1 Tab1:** Assessments and instruments used in the PETRA study

Outcomes	Instrument	t0	t1	t2	t3	t4	t5	t6
Primary endpoint								
Overall 2-year survival	Medical log (ongoing assessment)							
Secondary endpoints								
2-year non-relapse mortality, median (disease-free) survival	Medical log (ongoing assessment)							
Quality of life	EORTC QLQ30 / HDC-29 module	X	X	X	X	X	X	X
Fatigue	Multidimensional Fatigue Inventory (MFI)	X	X	X	X	X	X	X
Muscle strength	Isometric and isokinetic strength of representative muscle groups for upper and lower extremity measured at the IsoMed2000®	X			X		X	X
	Hand-Held-Dynamometer (isometric)	X	X	X	X	X	X	X
Cardiorespiratory fitness	CPET (VO_2_peak)	X			X		X	X
	6-min Walk Test	X	X	X	X	X	X	X
Body composition	bioelectrical impedance analysis, weight, height	X	X	X	X	X	X	X
Physical Activity	Accelerometry	X		X	X	X	X	X
Depression	CES-D	X	X	X	X	X	X	X
Distress	NCCN-Distress	X	X	X	X	X	X	X
Locus of control	KKG (German)	X	X	X	X	X	X	X
Cognitive function	Trail-making-test	X	X	X	X	X	X	X
Common side-effects	VAS, every week, later every 3 weeks							
Biomarker	Various methods (ELISA)	X	X	X	X	X	X	X
Oxidative stress marker	Analysed in urine samples	X	X	X	X	X	X	X
Others								
Socio-demographic factors	Recording of date of birth, education, occupation, familial situation, smoking, alcohol consumption	X					X	X
Medical history	Recording of pre-existing diseases, therapies	X						
Treatment data	Conditioning, complications		X					
Karnofsky Performance Score	Physician rating	X	X	X	X	X	X	X
Medication (immunosuppression, corticosteroids, analgesics)	Recorded at each visit/phone call on a medication log form	X	X	X	X	X	X	X
Physical activity history	Physical activity in adolescence, pre-diagnosis, during, and after intervention is recorded, including walking, cycling, and sports activities	X			X		X	X

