### Secondary outcomes

#### Non-relapse mortality and median survival

We will distinguish between 2-year non-relapse mortality (e.g. related to GvHD, sepsis), median survival and median disease-free survival. Survival data will be collected using medical logs and will be approved by the study physician (PD).

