### Data analysis

The main intervention effect will be assessed on the basis of a Cox-regression analysis between exercisers and controls (relaxation group) as defined at randomization, regardless of exercise adherence, i.e. according to the intent-to-treat principle.

The differences in secondary endpoints between groups will be assessed using mixed models, which accounts for repeated observations on the same subjects over time. This method provides a more efficient estimate of the intervention effect in pretest-post-test trials than traditional methods [74]. Mixed models will also be used for testing to which extent differences between the treatment groups depend on training adherence, changes in muscle strength, cardiorespiratory fitness, and body composition. Normality assumptions will be checked and, if deviation from normality is detected the data will be transformed accordingly.

In addition, change in physical activity behavior post intervention will be monitored on an explorative basis.

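### The mixed-model rule for secondary endpoints has no exception, yet three listed secondary endpoints (non-relapse mortality, median survival, disease-free survival) are once-only, possibly censored events it cannot analyse

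*Protocol article*

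**What the plan says.** The Data analysis section contains two assignments of method. For the primary comparison: "The main intervention effect will be assessed on the basis of a Cox-regression analysis between exercisers and controls". For the rest: "The differences in secondary endpoints between groups will be assessed using mixed models"; the sentence goes on to say that such models allow for several measurements in one patient. No secondary endpoint is excepted. The text then supports the choice by saying that mixed models give a "more efficient estimate of the intervention effect in pretest-post-test trials than traditional methods", and adds a distributional safeguard: "Normality assumptions will be checked and, if deviation from normality is detected the data will be transformed accordingly".

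The list of secondary endpoints opens with survival outcomes. The abstract has "secondary endpoints are non-relapse mortality, median survival, patient reported outcomes". The Objectives section again places 2-year non-relapse mortality and median survival first among the secondary objectives. Table 1, under its secondary endpoints, has the row "2-year non-relapse mortality, median (disease-free) survival", collected continuously through the medical log. The section on non-relapse mortality and median survival, itself under Secondary outcomes, says: "We will distinguish between 2-year non-relapse mortality (e.g. related to GvHD, sepsis), median survival and median disease-free survival".

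**The concern.** A mixed model for repeated observations needs a response measured several times in the same patient. The version described here also needs a baseline value and a roughly normal (or transformable) distribution. Death without relapse, death from any cause, and relapse or death have none of these features. They are times to a single event, unknown for patients whose follow-up ends first.

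Non-relapse mortality also needs a decision on relapse. As the term is ordinarily used, a patient who has relapsed can no longer have a non-relapse death, so relapse is a competing event.

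The endpoint is not peripheral. The Background and the Discussion both cite the group's earlier trial for a non-relapse mortality of 4 vs 13 % (p = .017) as part of the case for this study. If the published rule cannot be applied, the method for this comparison has to be chosen elsewhere. Naive Kaplan-Meier, cause-specific hazard and subdistribution analyses answer different questions and can disagree, so the choice should be fixed before outcome data are examined.

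**Working it through.** The point concerns the choice of method, so the check is mainly a comparison of passages.

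**1. What the rule requires.** From the Data analysis section: (a) repeated observations per patient; (b) a pre-intervention and a post-intervention value; (c) a response for which normality, possibly after transformation, makes sense.

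**2. What the endpoints offer.**

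| Secondary endpoint | Repeated values | Baseline value | Normality meaningful | Can be censored |
|---|---|---|---|---|
| Quality of life, fatigue, depression, distress, strength, 6-min walk, body composition, biomarkers | Yes, visits marked in Table 1 | Yes, t0 | Yes, or after transformation | No; missing values instead |
| Symptom scales (VAS) | Yes, weekly, later at phone calls | Not marked in Table 1 | Possibly | No; missing values instead |
| 2-year non-relapse mortality | No, at most one event | No | No | Yes |
| Median survival | No, at most one event | No | No | Yes |
| Median disease-free survival | No, at most one event | No | No | Yes |

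The last three come from the medical log and have no t0–t6 marks in Table 1. They fail (a), (b) and (c).

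**3. Could a looser reading rescue the rule?** Suppose follow-up to two years were complete and non-relapse mortality were analysed as yes or no. Each patient would still contribute one value and no baseline, so the stated reason for a mixed model would not apply. No transformation makes a single binary or censored outcome normal.

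**4. Does another sentence supply the method?** Cox regression is tied to the main intervention effect. The log-rank test appears only in the Sample size section, for two-year overall survival. Neither is extended to the secondary survival endpoints. Median survival is the mildest case, because it summarises the same survival experience that the primary Cox model compares.

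**5. Is the primary analysis touched?** The stated sample size can be reproduced without reference to the secondary endpoints.

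- Inputs (Sample size section): two-year survival 0.66 and 0.49, two-sided α = 0.05, power 0.80, equal groups.
- Hazard ratio (proportional hazards) = ln 0.66 / ln 0.49 = 0.582.
- Events (Schoenfeld) = (1.960 + 0.842)² / (0.25 × (ln 0.582)²) = 107.5, rounded up to 108.
- Mean event probability = 1 − (0.66 + 0.49)/2 = 0.425.
- Patients = 108 / 0.425 = 254.1, rounded up to 255, against 256 stated.

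The figure holds and nothing here alters it.

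**The case against.** The strongest reply is that this is loose wording in a condensed article. The sentence describes its models as handling repeated observations, the justification speaks of before-and-after trials, and the safeguard is a normality check. All of that fits only outcomes measured at visits, and Table 1 already separates those from the medical-log outcomes. A reader might infer that the investigators mean to fit a repeated-measures model to deaths. The documents do not support that: the word all does not appear, and the surrounding text suggests a narrower intention. What remains is that the rule as written names no exception, and no passage limits it to the repeatedly measured outcomes.

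A second reply is that the handling of relapse is the kind of detail left to a full protocol or analysis plan, neither of which is shown. That is right, and silence on competing risks would not be a finding by itself. The finding rests on a stated method that does not fit endpoints the article lists.

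Two stronger readings should also be resisted.

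- **A quantified bias.** One could compute how far one-minus-Kaplan-Meier with relapse censored overstates non-relapse mortality. The protocol never proposes that estimator, and it gives no relapse rate, so any figure rests on assumptions. It would also mix a bias in the level with a contrast between arms. Applied to the quoted 4 vs 13 %, with constant hazards and relapse assumed at 30 % in both arms, h = −ln(1 − relapse − NRM) × NRM/(relapse + NRM) and 1 − exp(−h) give 4.8 vs 15.6 %. The contrast moves only from 9.0 to about 10.9 points. This is an illustration and carries no weight in the conclusion.
- **Extension to GvHD onset.** The section on side-effects has attending physicians record GvHD severity and duration every week. Onset is not a stated endpoint, and weekly severity is a repeated measure for which a mixed model is conceivable.

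**Conclusion.** The point holds as a misassigned method. The rule for secondary endpoints, taken as written, cannot analyse 2-year non-relapse mortality, median survival or median disease-free survival, all of which the article classes as secondary.

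The severity is moderate. The primary endpoint has a suitable intention-to-treat Cox analysis, the sample size is unaffected, and the rule suits the repeatedly measured outcomes. No size of bias is claimed, because the documents give neither a relapse rate nor an estimator for non-relapse mortality.

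The conclusion assumes that non-relapse mortality has its usual meaning, so that relapse precludes it, and that the mixed models are the ordinary repeated-measures kind, as the normality check indicates. An analysis plan, not shown, may already name suitable methods; the published sentence would then still need to be brought into line.

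**What to change.** - Limit the mixed-model sentence to the repeatedly measured outcomes: questionnaires, fitness, body composition, biomarkers and symptom scales.
- Analyse median survival and disease-free survival by Kaplan-Meier, with a log-rank test or Cox regression for the group comparison.
- Estimate 2-year non-relapse mortality by cumulative incidence with relapse as a competing event. Compare groups with a cause-specific Cox model, supplemented by Gray's test or a Fine-Gray model, and state which comparison leads.
- Settle this before outcome data are examined.

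The cost is a few sentences and a little programming. Survival data are already collected through the medical log, and disease-free survival already requires relapse status. Data collection, sample size and the primary analysis stay as they are.

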## Discussion

Treating hematological malignant diseases with allo-HCT is highly demanding for patients who experience numerous side-effects and face a very high risk of severe treatment related complications, such as GvHD and severe infections, both in the short and long-term. In general, survival rates after allo-HCT are relatively low.

Recently, our group demonstrated that there may be a positive effect of exercise on survival after allo-HCT. In our first RCT we observed a significant reduced total mortality for the experimental group (12 vs. 28 %, *p* = .034) and for NRM (4 vs. 13 %, *p* = .017). Furthermore, we observed that physical fitness prior transplantation was highly protective against NRM [35]. The cohort study by Wood et al. also suggests an association between fitness level prior transplantation and risk of mortality [33], but a small sample size of 22 patients and no use of multivariate models hamper the interpretation of these results. Against this background we designed the PETRA study. PETRA will add to current knowledge on exercise in allo-HCT patients with respect to several aspects: (1) Effect of yearlong exercise intervention on prognosis; (2) exercise effect on side-effects and complications, e.g. physical performance, QoL, fatigue; (3) exercise effect on GvHD and hematological/immunological reconstitution; and (4) sustainability and long-term effects of exercise intervention.

Given the indication of reducing mortality in cancer survivors by an appropriate physical active lifestyle, the question about possible mechanisms occurs. Some evidence suggests several potential mechanisms underlying [30]. One discussed mechanism is inflammation [75]. Several trials reported that exercise can reduce C-reactive protein (CRP), which is a marker of chronic inflammation [76–78] and change Interleukin-6 (IL-6) levels. IL-6 produced by muscle fibers during and after exercise stimulates the circulation of anti-inflammatory cytokines, such as IL-1ra and IL-10 and inhibits the production of tumor necrosis factor alpha (TNF-α) [79]. In a prospective cohort study in breast cancer patients, elevated CRP and serum amyloid A were associated with reduced overall survival [80]. Furthermore, when exercise potentially can influence parts of the immune system, the question arises, if a GvHD reaction in allo-HCT patients can also be influenced by exercise. To our knowledge, no intervention study in humans investigated a possible association between exercise and severity of the major side-effect GVHD. New results from mice experiments suggest that physical exercise can have a positive impact on GvHD. The researchers showed that endurance training (5 times per week) in mice was beneficial with regard to overall survival and also alters GvHD symptom severity. Furthermore, the authors revealed possible pathways for altering GvHD by demonstrating that exercising mice had lower levels of anti-inflammatory cytokines (IL-4 and TNF-α) [81]. Based on these findings, we aim to investigate whether exercise is able to alter GvHD severity in human adults. We are further interested to elucidate other possible exercise pathways altering GvHD by investigation of endothelial markers. Markers of interest are blood biomarkers of inflammation and TNF-α as well as endothelial markers and hepatocyte growth factor [82–85]. Natural killer cells (NK-cells) have also been shown to modulate acute GvHD, infections and recurrence [86, 87]. The positive effect of exercise on NK-cell activity in cancer patients could already be shown in studies [88], and a review about NK-cells and exercise suggests exercise as an adjunct therapy to promote expansion of NK-cell subsets [89]. Interestingly, one RCT in allo-HCT patients could already observe a positive effect of exercise during transplantation process on lymphocyte count [90].

Additionally, restoring the function of the entire haematological system after allo-HCT is an important prognostic indicator [91, 92]. Therefore, we focus also on exercise effects on haematological recovery after allo-HCT. A potential positive effect on the haematological system e.g. lymphocytes, haemoglobin could already be shown [8, 90, 93].

A central secondary endpoint is cancer-related fatigue. Fatigue is described as the most distressing side effect in cancer treatment, however, the pathophysiology of fatigue and the possible positive effect of exercise on its prevention/therapy are not well understood [94]. Therefore, our trial enables investigation of the effects of exercise on immunologic parameters as well as on biomarkers of inflammation and oxidative stress as possible mediators of fatigue [95, 96]. However, not only fatigue is a common side-effect. As a consequence of longer periods of drug intake, e.g. immune suppression and antibiotics, patients often suffer from nausea, diarrhea and further complaints. Recent studies indicated a better symptom control in exercising patients [97].

Our decision of choosing an intervention period of one year was based on the consideration that the recovery period after allo-HCT can take months to years. However, even years after allo-HCT patients have an increased risk to develop co-morbid conditions, e.g. metabolic or cardiovascular diseases [22]. On one hand, emerging research evidence indicates that these life style diseases are associated with physical inactivity. On the other hand, studies show that hematological cancer survivors are less likely to be physically active. Moreover, changing exercise behavior requires longer, individually adapted interventions. To enhance motivation and adherence, the PETRA study uses goal setting methods, and individual barriers are discussed during regular phone calls. These components have been shown to improve adherence [71]. Furthermore, PETRA helps patients to integrate in an exercise facility close to their home or give them the possibility to perform an internet-based training program. All these efforts may help patients to change the physical activity behavior in the long term. Finally, if during or at the end of the exercise intervention beneficial effects are detected, it is of interest whether those benefits sustain over a longer period of time.

Strengths of the PETRA study are the rigorous study design with a large sample size, adequately powered for the primary endpoint survival, and a broad range of assessments, including gold-standard methods for physical fitness and physical activity. Therefore, PETRA provides a unique opportunity to examine the interaction of exercise/ physical activity on the haematological system and GvHD reaction. A further strength is the choice of the control group (relaxation training). Previous exercise RCT used typically *usual care* as comparison groups. Thus, it is unclear to what extent the observed effects are based on the physical exercise effect itself, or rather on psycho-social factors related to social support or attention by the trainer. This factor is particularly important when psychosocial outcomes are measured.

## Conclusion

Previous studies in allo-HCT patients established first evidence about beneficial effects of exercise interventions on physical and psychosocial outcomes. However, the focus changed to more clinically relevant endpoints, e.g. prognosis. To our knowledge, no study has yet investigated a possible effect of exercise on overall survival after allo-HCT. Furthermore, there is a need for a better understanding of the physiological and psychological effects of exercise and their biological mechanisms in patients during and after allo-HCT. The PETRA study will provide a comprehensive picture of the potential effects of exercise during and after allo-HCT on overall survival, reducing side-effects and complications, and improving quality of life. We anticipate that our study will help to refine exercise guidelines for allo-HCT patients.

## Abbreviations

ACSM: American College of Sports Medicine
AEs: Adverse events
BIA: Bioelectrical impedance analysis
CRP: C-reactive protein
CPET: Cardiopulmonary exercise test
GvHD: Graft-versus-host disease
IL-6: Interleukin-6
KPS: Karnofsky Peformance Scale
MFI: Multidimensional Fatigue Inventory
NCCN: National Comprehensive Cancer Network
NRM: Non-relapse mortality
QoL: Quality of life
RCTs: Randomized controlled trials
SAEs: Serious adverse events
TM: Total mortality
TNF-α: Tumor necrosis factor alpha
VO2peak: Maximum oxygen uptake
